### Objectives and hypotheses

2.1

This study aims to evaluate the effectiveness of the mobile self-help application “SleepQ” as an adjunct to standard care for individuals with chronic insomnia in routine outpatient settings, within a superiority trial framework. The intervention is based on dCBT-I and is designed to address core insomnia symptoms through structured behavioral and cognitive strategies. We hypothesize that participants receiving dCBT-I in addition to standard care will show greater reductions in self-reported insomnia severity compared to the waitlist control group (CG) after 6 weeks of intervention.

As secondary objectives, we hypothesize that dCBT-I will lead to greater improvements across several additional domains compared to the CG. Specifically, we expect that participants in the intervention group will report greater reductions in maladaptive sleep beliefs, daytime sleepiness, and depressive and anxiety symptoms, along with improved work productivity and health-related quality of life. Furthermore, we will assess the stability of treatment effects in the intervention group at 3- and 6-month follow-ups. Exploratory analyses will examine app-based sleep diary parameters, user adherence, and engagement with the intervention.

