### Measures

2.4

Assessments will take place at screening/baseline (t0), 2 weeks after baseline (t1), 4 weeks after baseline (t2), and 6 weeks after baseline (t3, post-treatment). Additionally, participants in the IG will undergo follow-up assessments at 3 months (t4) and 6 months (t5) post-randomization. Assessments at t1, t2, t4, and t5 will be conducted remotely, while screening (t0) and post-treatment (t3) assessments will take place in person. An overview of the clinical outcome measures over time, based on the Standard Protocol Items: Recommendations for Interventional Trials (SPIRIT) 2013 guidelines, is provided in Table 2.

**Table 2 t0010:** Schedule of enrolment, interventions, and assessments according to SPIRIT.

	STUDY PERIOD						
Study period	Enrolment	Allocation	Post-allocation			Follow up	
Timepoint	*-t*_*1*_	*t*_*0*_	*t*_*1*_	*t*_*2*_	*t*_*3*_	*t*_*4*_	*t*_*5*_
Week		0	*2*	*4*	*6*	*12*	*24*
Enrolment							
Informed consent	X						
Eligibility screen	X						
Clinical Interviews	X						
Allocation		X					
Interventions							
Intervention Group: Digital cognitive behavioral therapy for insomnia		X	X	X	X		
Control Group: Waitlist control		X	X	X	X		
Assessments							
Demographic and clinical information		X					
Primary outcome							
ISI		X	X	X	X	X^a^	X^a^
Secondary outcomes							
ESS		X	X	X	X	X^a^	X^a^
DBAS-16		X	X	X	X	X^a^	X^a^
PHQ-9		X	X	X	X	X^a^	X^a^
GAD-7		X	X	X	X	X^a^	X^a^
SF-36		X	X	X	X		X^a^
WPAI-SHP		X	X	X	X		X^a^
Other measures							
Sleep parameters from sleep diary: SE, TST, SOL, WASO			X^a^	X^a^	X^a^		
SUS					X^a^		
App satisfaction questionnaire					X^a^		
App usage compliance					X^a^		
Adverse event			X	X	X		
Concomitant medication assessment			X	X	X	X^a^	X^a^
Concomitant therapy assessment			X	X	X	X^a^	X^a^

Abbreviations: ISI, Insomnia Severity Index; ESS, Epworth Sleepiness Scale; DBAS-16, Dysfunctional Beliefs and Attitudes about Sleep-16; PHQ-9, Patient Health Questionnaire-9; GAD-7, Generalized Anxiety Disorder-7; SF-36, Short Form-36; WPAI-SHP, Work Productivity and Activity Impairment Questionnaire–Specific Health Problem; SUS, System Usability Scale; SE, sleep efficiency; TST, total sleep time; SOL, sleep onset latency; WASO, wake after sleep onset.

a Only administered to intervention-group.

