### Planned statistical analysis

2.6

The analysis will include participants following the full analysis set based on the Intention-to-Treat principle, which includes all randomized participants who have completed a baseline assessment of the primary outcome (ISI score). All statistical analyses will be performed using SAS Software Version 9.4 or higher, with a two-sided significance level of 0.05.

Descriptive statistics will summarize baseline demographic and clinical characteristics, adherence, and usability measures. Depending on their distribution, continuous variables will be reported as means and standard deviations or medians and interquartile ranges, while categorical variables will be presented as frequencies and percentages.

To evaluate the primary outcome at post-treatment (t3, 6 weeks), an Analysis of Covariance (ANCOVA) will be conducted, adjusting for baseline values and stratification factors (study site and sleep medication use) as covariates to compare differences between the IG and the CG. Effect sizes (Cohen's d) will be reported alongside *p*-values and confidence intervals to indicate the magnitude of between-group differences. A mixed-effects model for repeated measures (MMRM) will be applied to assess longitudinal treatment effects. This model considers three repeated assessments (t1, t2, t3) as nested within individuals, accounting for intra-individual correlations and missing data. No imputation of missing values is planned, as MMRM accommodates missing data under the assumption that data are missing at random. A stepwise modeling approach will be used, beginning with a random intercept model without predictors. Next, fixed effects for time (study entrance, 2 weeks, 4 weeks) and treatment (IG vs. CG) will be added. Finally, a treatment × time interaction term will be introduced to examine whether outcome trajectories differ between groups. Treatment effects will be reported using Cohen's d as a measure of effect size. Descriptive analyses will be conducted to explore patterns of missingness, including comparisons of baseline characteristics between study completers and non-completers, as well as the timing and extent of dropout across timepoints.

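### The supportive MMRM is given two conflicting visit sets, and under neither does its treatment × time interaction test the week-6 group difference

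*Protocol article*

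**What the plan says.** Section 2.6 (Planned statistical analysis) gives the primary comparison to a single-visit model: "To evaluate the primary outcome at post-treatment (t3, 6 weeks), an Analysis of Covariance (ANCOVA) will be conducted", adjusted for baseline and the stratification factors. It then adds an MMRM that "will be applied to assess longitudinal treatment effects".

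Two sentences fix the visits of that MMRM, and they differ:

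- "This model considers three repeated assessments (t1, t2, t3) as nested within individuals". Section 2.4 and Table 2 put t1, t2 and t3 at weeks 2, 4 and 6, all after baseline.
- In the stepwise build, "fixed effects for time (study entrance, 2 weeks, 4 weeks) and treatment (IG vs. CG) will be added". This list includes baseline and omits week 6.

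The build then closes: "Finally, a treatment × time interaction term will be introduced to examine whether outcome trajectories differ between groups". Cohen's d is promised for treatment effects, but the MMRM contrast or visit it refers to is not stated. Section 2.1 words the secondary aims as improvement relative to control: "we hypothesize that dCBT-I will lead to greater improvements across several additional domains compared to the CG".

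**The concern.** The hypotheses concern greater improvement from baseline than in the control group. Under randomisation the expected baseline difference is zero, so the matching null is that the IG-CG difference is zero at weeks 2, 4 and 6. An interaction fitted to post-baseline visits alone has a weaker null: that the difference is the same at all three visits. A treatment that works by week 2 and keeps working satisfies that null exactly. Its result could then be reported as no difference in trajectories beside a positive primary ANCOVA.

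The other list avoids this but drops the visit at which treatment ends and the primary outcome is read. On either reading the interaction is not a test of the week-6 difference. This matters because the MMRM is also the protocol's stated answer to missing data, with 20% attrition expected (section 2.7). It can serve that purpose at week 6 only if a week-6 contrast is taken from it.

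**Working it through.** The plan states no figure for this analysis, so there is none to reproduce.

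**Inputs from the protocol.** Tests are made "with a two-sided significance level of 0.05". The target is 120 participants, allocated 1:1, with 20% attrition: 120 × 0.80 = 96, or n = 48 per arm. The planning effect is f = 0.485; for two equal groups d = 2f = 0.97.

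**Assumed, not in the documents.** SD of 1 at every visit, equal correlation ρ between all visits (0.5 and 0.7), zero baseline difference, complete data on the 48 per arm, and 0.5 SD as a smaller effect.

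**Formulas.** With δⱼ the IG-CG difference at visit j and δ̄ its mean over the visits in the model, the noncentrality λ is:

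- Treatment × time interaction: λ = (n/2) · Σ(δⱼ − δ̄)² / (1 − ρ), with 2 df for three visits.
- Treatment main effect averaged over weeks 2, 4 and 6 (no baseline adjustment): λ = (n/2) · δ̄² / [(1 + 2ρ)/3].
- Baseline-adjusted week-6 contrast: λ = (n/2) · δ₃² / (1 − ρ²).

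Power then follows from the noncentral F distribution. Worked cases at ρ = 0.5:

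- Constant 0.97 at weeks 2, 4 and 6: every δⱼ equals δ̄, so λ = 0 and the interaction rejects at 5%. This does not depend on ρ, n or the size of the effect.
- Linear growth 0.323, 0.647, 0.970: δ̄ = 0.647, Σ = 2 × 0.3233² = 0.2091, λ = 24 × 0.2091/0.5 = 10.0, power 81%.
- Constant 0.5 with visits 0, 2 and 4: differences 0, 0.5, 0.5, Σ = 0.1667, λ = 24 × 0.1667/0.5 = 8.0, power 71%.
- Week-6 contrast at 0.5: λ = 24 × 0.25/0.75 = 8.0 on 1 df, power 80%.

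Power in %, ρ = 0.5 / ρ = 0.7:

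| Difference at weeks 2, 4, 6 (SD) | Interaction, weeks 2, 4, 6 | Interaction, weeks 0, 2, 4 | Averaged main effect | Week-6 contrast |
|---|---|---|---|---|
| 0.97, 0.97, 0.97 | 5 / 5 | >99 / >99 | >99 / >99 | >99 / >99 |
| 0.80, 0.90, 0.97 | 11 / 15 | 99 / >99 | >99 / >99 | >99 / >99 |
| 0.65, 0.85, 0.97 | 27 / 43 | 98 / >99 | >99 / 99 | >99 / >99 |
| 0.32, 0.65, 0.97 | 81 / 96 | 81 / 96 | 97 / 94 | >99 / >99 |
| 0.50, 0.50, 0.50 | 5 / 5 | 71 / 91 | 84 / 77 | 80 / 92 |
| 0.30, 0.40, 0.50 | 13 / 19 | 42 / 64 | 66 / 58 | 80 / 92 |

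At ρ = 0.3 the interaction over weeks 2, 4 and 6 falls to about 66% for linear growth to 0.97 and stays at 5% for any constant effect. The interaction over weeks 0, 2 and 4 does detect an early benefit, but it contains no week-6 data.

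**The case against.** A reader might infer that the protocol uses the interaction to decide whether treatment works, and so could miss a real effect. The text does not support that. The interaction is introduced only to examine trajectories; the efficacy question goes to the baseline-adjusted week-6 ANCOVA, which none of this touches. The treatment main effect enters one step earlier and would show a constant benefit. A null interaction beside a positive ANCOVA is also no contradiction: it says the benefit was stable after week 2. These points stand, and they limit the consequence to interpretation. The table therefore compares tests of different hypotheses and does not show power lost on the trial's primary question.

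Three further points have some force. First, an effect complete by week 2 may not be typical of a programme whose modules are delivered in sequence; with linear growth to 0.97 SD the interaction does well. The protocol gives no weekly timing of effect, however, and a partly early effect (0.65, 0.85, 0.97) already cuts its power to 27 to 43%. Second, a reader might infer that benefits on the secondary scales would be reported as absent. Section 2.6 assigns no model to those scales, so that harm is conditional on the same model being used. Third, the choice of contrast from a supportive MMRM is commonly left to the SAP. That answers a complaint of missing detail, but not two incompatible visit lists in one paragraph.

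The main effect is only a partial remedy. It averages weeks 2, 4 and 6, comes from an intermediate model, and is not the week-6 difference.

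**Conclusion.** The point holds as a defect of the supportive analysis. The two visit lists in section 2.6 cannot both be right. Under weeks 2, 4 and 6, the interaction has exactly zero noncentrality for a sustained constant benefit (5% rejection); this is algebra and needs no assumption about correlation. Under study entrance, week 2 and week 4, an early benefit is detectable (71 to 91% at a constant 0.5 SD, more than 99% at 0.97 SD), but the post-treatment visit is absent. The other percentages rest on equal SDs, equal correlation of 0.5 to 0.7 and 48 per arm with complete data. The primary conclusion is not at risk. What is at risk is the reading of the longitudinal analysis, and of the secondary outcomes if they share the model.

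**What to change.** In section 2.6:

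- State one visit set: weeks 2, 4 and 6 as outcomes, with the baseline value and the stratification factors as covariates. Delete the conflicting list.
- Name the MMRM treatment effect: the adjusted IG-CG difference at week 6 from the model with treatment, visit and treatment × visit, with the differences at weeks 2 and 4 also shown. Tie the reported Cohen's d to that contrast.
- If an overall test is wanted, use the joint 3-df test that the difference is zero at all three visits.
- Keep treatment × visit in the model, but describe its p-value only as a test of whether the effect changes over time.

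The cost is one or two sentences and one contrast statement in SAS. No new data or participants are needed, and the primary analysis is unchanged.

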### Statistical power and sample size

2.7

The sample size was determined using G*Power 3.1 (Faul et al., 2007), based on an ANCOVA with a fixed-effects model, assuming a large effect size (Cohen's f = 0.485) derived from previous research, which reported heterogeneous effect sizes ranging from 0.97 to 2.08 (Cohen's d) (Behrendt et al., 2020; Schuffelen et al., 2023). Cohen's f is the conventional effect size metric for ANCOVA models, and can be derived from Cohen's d. The calculation was conducted with an alpha level of 0.05, a statistical power (1- beta) of 0.90, and 3 covariates, including baseline scores and stratification factors. The G*Power analysis indicated that a total sample size of 97 participants would be required to achieve the desired power. The required sample size was adjusted to account for a 20 % attrition rate, resulting in a final target of 120 participants.

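### The sample size of 97 does not follow from the stated inputs: for a two-arm ANCOVA with f = 0.485 and 90% power they give 47, so the justification needs correcting although the trial is not short of power

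*Protocol article*

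**What the plan says.** Section 2.7 (Statistical power and sample size) describes a G*Power 3.1 calculation "based on an ANCOVA with a fixed-effects model", "assuming a large effect size (Cohen's f = 0.485"), drawn from earlier work with "heterogeneous effect sizes ranging from 0.97 to 2.08 (Cohen's d"). The other inputs are "an alpha level of 0.05, a statistical power (1- beta) of 0.90" and "3 covariates, including baseline scores and stratification factors". The output is given as: "The G*Power analysis indicated that a total sample size of 97 participants would be required to achieve the desired power". A 20% attrition allowance follows, "resulting in a final target of 120 participants".

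Section 2.3 (Trial design) fixes two arms with 1:1 allocation. Section 2.6 (Planned statistical analysis) makes the primary analysis an ANCOVA of the 6-week ISI between those two arms, adjusted for baseline, study site and sleep medication use, "with a two-sided significance level of 0.05". The numerator degrees of freedom entered in G*Power are not printed.

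**The concern.** The paragraph prints both the inputs and the output, so it can be checked, and the two do not agree. An effect of almost one standard deviation between two equal groups needs fewer than 50 participants for 90% power, and the stated requirement is about twice that.

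The paragraph is the article's only justification for the number enrolled. As written, it ties 97 participants to 90% power at d = 0.97, whereas that number gives 90% power at a much smaller effect. Anyone who reruns the calculation will fail to reproduce it, and a results paper that repeats the paragraph would carry the error forward.

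**Working it through.** **Inputs**
- From section 2.7: f = 0.485, alpha = 0.05, power = 0.90, 3 covariates, stated N = 97, attrition 20%, target 120.
- From sections 2.3 and 2.6: two groups, 1:1, one between-group contrast, two-sided 0.05. The numerator df is therefore 2 − 1 = 1. It is not printed, but the design fixes it.
- For two equal groups d = 2f, so d = 2 × 0.485 = 0.97, the low end of the cited range.

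**Formula** (the G*Power fixed-effects ANCOVA). Power is the probability that a noncentral F variable exceeds the 5% critical value of F(df1, df2), with noncentrality λ = f²N and df2 = N − groups − covariates.

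**Attempt to reproduce 97.** With df1 = 1, f² = 0.485² = 0.235225 and df2 = N − 5:

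| N | λ = 0.235225 × N | df2 | Power at f = 0.485 |
|---|---|---|---|
| 46 | 10.82 | 41 | 0.895 |
| 47 | 11.06 | 42 | 0.901 |
| 96 | 22.58 | 91 | 0.9969 |
| 97 | 22.82 | 92 | 0.9972 |
| 120 | 28.23 | 115 | 0.9995 |

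The smallest N with power of at least 0.90 is 47. As a cross-check, the exact two-sample t test at d = 0.97 gives 46.7 in total, and the normal approximation gives 23 per arm, or 46.

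**Variations**
- Covariates, df1 = 1: the required N is 47 with 0 to 3 or 6 covariates, and 48 with 7 (baseline 1 + six sites as 5 dummies + medication 1).
- Power, df1 = 1: 0.80 gives 36, 0.95 gives 58, 0.99 gives 81.
- Alpha, df1 = 1, power 0.90: 0.025 gives 56, 0.01 gives 67.
- Reading 0.485 as d rather than f (f = 0.2425) gives 181.
- Numerator df, other inputs as stated: 1 gives 47, 2 gives 58, 3 gives 65, 5 gives 76, 10 gives 97, 11 gives 100.

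With the stated f, alpha, power, two groups and 3 covariates, only df1 = 10 returns 97. A two-arm treatment contrast cannot have 10 numerator df.

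**What the planned numbers deliver** (df1 = 1, 3 covariates)

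| Completers | 90% power at | 80% power at |
|---|---|---|
| 96 | f = 0.334, d = 0.67 | f = 0.289, d = 0.58 |
| 97 | f = 0.333, d = 0.67 | f = 0.287, d = 0.57 |

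**Attrition.** 47/0.8 = 58.75, so 59; 48/0.8 = 60. For the plan's own figure, 97/0.8 = 121.25, so 122 against the stated 120; 120 × 0.8 = 96, one below 97.

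**The case against.** The strongest defence is that nothing in the trial suffers. The error runs in the safe direction, and type I error, the primary analysis and enrolment are untouched. That stands, and it sets the weight of the point. It does not make the sentence correct, because the article says 97 are required for the stated power. A journal article may leave details to a fuller document, but here the inputs and the output are both printed, and the one missing input is fixed by the two-arm design.

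A reader might infer more than the text supports:
- **That the trial lacks the power it claims.** It does not. Power for f = 0.485 is well above 90% at the planned numbers.
- **That the detectable effect is misreported.** Section 2.7 gives a planning effect and states no minimum detectable effect. A modest or null result would be read from the estimate and confidence interval that section 2.6 commits to reporting.
- **That the covariate count and the attrition step are further errors of substance.** Three is a fair count of the named variables, and using 7 df moves N by one. The gap between 120 and 122 is immaterial: power at f = 0.485 is 0.9969 with 96 completers and 0.9972 with 97.
- **That a wrong df was entered.** The match at df1 = 10 is a back-calculation. It makes a slip plausible but does not establish one.

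**Conclusion.** The point holds. With the printed inputs and the two-arm contrast, the required total is 47 (48 with site as dummy variables), not 97, an overstatement by a factor of about two (97/47 = 2.06). After 20% attrition the figure is 59 to 60, against 120 enrolled.

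This rests on numerator df = 1, which follows from the design, and on f defined as G*Power defines it, with d = 2f for equal groups. No variation of covariate count, alpha or power listed above brings the answer to 97 while the numerator df is 1.

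It is a correction to the stated justification and does not threaten the trial's validity.

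**What to change.** Keep 120 enrolled and rewrite the calculation in section 2.7, stating numerator df = 1 and the covariate df used. Either of two wordings would be consistent:
1. For f = 0.485 (d = 0.97), 90% power needs 47 participants (48 with site as five dummy variables), or 59 to 60 with 20% attrition; the target of 120 is larger by choice, with the reason given.
2. With 120 randomised and 20% attrition, 96 completers give 90% power for f of about 0.33 (d of about 0.67) and over 99% power for d = 0.97.

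The second describes the trial as it will be run and also removes the attrition rounding mismatch. Neither wording should attribute 97 to f = 0.485 at 90% power. If the original G*Power output is on file, checking its numerator df would settle the cause.

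The cost is one rewritten paragraph, with no change to enrolment, analysis or conduct.

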## Discussion

3

This study protocol outlines a multicenter RCT evaluating the effectiveness of a mobile-based dCBT-I intervention compared to a waitlist control group. The intervention, approved as a PDT by the Korean MFDS, aims to address barriers to access to insomnia treatment by providing a scalable and evidence-based solution. The study will assess the effects of short-term (6 weeks) and long-term (3 and 6 months) treatment using validated patient-reported outcomes, including the ISI as the primary outcome. Secondary outcomes will evaluate changes in maladaptive sleep beliefs, daytime sleepiness, depressive and anxiety symptoms, health-related quality of life, and work productivity. Additionally, exploratory analyses will examine intervention adherence, usability, and app satisfaction, contributing to a better understanding of dCBT-I engagement in routine care.

This trial has several methodological strengths. It is one of the first RCTs evaluating an MFDS-approved dCBT-I intervention in real-world clinical settings, increasing its clinical relevance. The multicenter design enhances generalizability across different healthcare settings. Including both short-term and long-term follow-up assessments allows for evaluating treatment durability beyond immediate symptom improvements. Sleep diary data and application usage metrics also complement self-reported outcomes, comprehensively evaluating intervention effects. The study's broad eligibility criteria improve generalizability to routine clinical settings (Schuffelen et al., 2023; Maurer et al., n.d.).

Despite its strengths, the study has several limitations. Due to the open-label design, participants will be aware of their group allocation, which may introduce expectation bias. However, blinding was not feasible given the nature of the intervention, and data analysis will be conducted by an independent researcher blinded to group allocation to minimize potential bias. Another limitation is the use of a waitlist control group instead of an active comparator, which does not account for placebo effects or non-specific therapeutic effects. Future research should compare dCBT-I to in-person CBT-I or pharmacological treatments to determine comparative effectiveness (Kallestad et al., 2021).

Furthermore, participant engagement with the intervention may vary, and adherence challenges could impact treatment outcomes. To address this, intervention adherence will be monitored using app log data, and dropout analyses will be conducted to examine potential patterns of non-completion (Gupta, 2011). The study includes individuals with coexisting psychiatric disorders, which increases relevance to real-world clinical populations but may introduce greater heterogeneity in treatment response (Klein et al., 2013). Also several exclusion criteria, such as recent use of non-pharmacological treatments, unstable medication regimens, or co-morbid sleep disorders, were necessary to minimize confounding and improve internal validity in evaluating treatment-specific effects. However, these restrictions may reduce the external validity of findings, as such characteristics are common among individuals seeking care for insomnia. Lastly, although including participants taking stable sleep medications enhances ecological validity, variations in concurrent pharmacological treatments may influence treatment effects (Klein et al., 2013; Krämer and Köhler, 2021). This will be addressed by including sleep medication use as a covariate in ANCOVA models and through exploratory subgroup analyses.

The primary manuscript and multiple supplementary articles containing trial results have been planned for this research. These will be published in journals relevant to the specific topic. Any modifications to the current protocol will be communicated upon article publication.

